#### Eating Disorder Inventory-2 (EDI-2) (Garner et al., 1983)

Eating disorder inventory-2 consists of 64 questions related specifically to eating behaviors, body perception as well as more general questions about attitudes, behaviors, and emotions. A total sum score and eight subscores are calculated (Nevonen and Broberg, 2001).

#### Inventory of Interpersonal Problems (IIP-32) (Horowitz et al., 1988)

Inventory of interpersonal problems consists of 64 questions with eight subscales assessing interpersonal problems.

#### The Beck Depression Inventory II (BDI) (Beck et al., 1996)

Beck depression inventory II is a 21-item self-report scale measuring degree of depressive symptoms.

#### Short Form Health Survey (SF-36) (Ware and Sherbourne, 1992)

Short form health survey assesses health-related quality of life and health status. It is a multidimensional instrument, with 36 questions to measure eight dimensions.

#### PTSD Symptom Scale-Self-Rating (PSS-SR) (Foa et al., 1993)

PTSD symptom scale-self-rating is a self-report outcome measure and contains 17 items assessing the severity of the PTSD symptoms described in the DSM-IV.

### Process Measurements/Mediators

#### Working Alliance Inventory-12 (WAI) (Hatcher and Gillaspy, 2006)

Working alliance inventory-12 assesses the bond between patient and therapist, and their agreement on tasks and goals of therapy.

#### Self-Compassion Scale (SCS) (Neff, 2003)

Self-compassion scale assesses the degree of self-compassion. Subscale scores for self-kindness, selfjudgment, common humanity, isolation, mindfulness, and over-identification. Self-compassion are computed by averaging across items within each subscale.

#### The Automatic Thoughts Questionnaire (ATQ) (Hollon and Kendall, 1980)

Automatic thoughts questionnaire is one of the most widely used instruments for measuring automatic thought. We used the 8-item version of the ATQ in this study because the short version showed internal consistency and validity equivalent to the original ATQ-30 (Netemeyer et al., 2002).

### Treatment Integrity

Both the therapists in the CFT treatment and the CBT treatment have received supervision from the architect behind the CFT condition ([name]) and the architect behind the CBT condition ([name]), respectively, since spring 2015 and will continue to receive biweekly supervision throughout the research period. All therapists will thus have the same training in either CBT or CFT and fidelity with model will be ensured by regular expert supervision. Individual therapy sessions will be videotaped and rated for treatment competence and adherence to the treatment protocol.

## Discussion

This paper has provided a description of a trial comparing two treatment models, its rationale and methods. The aims of the study, is to evaluate the effect of two treatment models, hence CFT and CBT on ED with or without childhood trauma and to study therapy processes important for treatment outcome for these patients. This is the first randomized trial of the effect of CFT for a transdiagnostic sample of ED. A large sample will be recruited among patients from outpatient clinics. Few exclusion criteria are applied and in this sense, the sample is clinically relevant and hence will enhance the external validity.

Each approach may yield efficacy for patients with ED without trauma. In that sense, it will provide support for CFT as an evidence supported treatments for EDs in addition to CBT. This is an important accomplishment given the complexity of these disorders. An important additional task is to examine if CFT could be more effective in reducing ED psychopathology, general symptoms and trauma symptoms and improving health-related quality of life for patients with additional childhood trauma experiences. By put forward knowledge of who responds best to which kind of treatment, we may offer help to a larger proportion of sufferers of ED.

In the present trial it is possible to explore the mediation effects of mechanisms. This will add to our knowledge about the relative effects of treatments for ED, compassion, cognitions, and therapeutic alliance. For EDs the influence of such mechanisms of change in CBT treatment is less established (Wilson et al., 2007; Horvath et al., 2011; Brauhardt et al., 2014; Wampold, 2015; Zaitsoff et al., 2015), and in CFT it is less studied due to the fact that the treatment is relatively new. However, there are a few of CFT mechanism studies (Kelly et al., 2013, 2014a,b), however, these are mostly correlational studies and therefore limited in drawing conclusions. Important research step is to observe session by session both the specific (self-compassion and cognitions) and generic (alliance) processes and ED symptoms throughout the whole treatment period.

Strengths of this RCT include the multilevel outcome measures, which comprise several psychological variables as well as follow-up up to 1 year after treatment. In addition, the protocol includes measures of treatment adherence and fidelity, thus enabling precise replications and weekly measurements which allows for an examination of temporal sequence. This allows some causal inferences. There are, however, limitation to consider given the chosen research design. The present study has no control condition, such as a no treatment, waiting-list or placebo. This could be a limitation especially if we do not detect a difference in outcome between the two treatment conditions. If no difference in outcome will be found, it will be difficult to decide to what extent the effect of treatment has to be ascribed to non-specific factors, the effect of testing, or time. However, we could argue that the level of spontaneous recovery in severe, enduring, treatment resistant and comorbid ED patients is low (Touyz and Hay, 2015; Treasure et al., 2015). In addition, comparing established treatments with no treatment or waitlist control group could be considered unethical for such a severe patient group (Devilly and McFarlane, 2009).

In addition, the therapist that provide the treatment in the two conditions belong to the same unit. Both the patients and the therapists meet each other in common meetings and meals at the unit and this can be the source of contamination between the groups. However, neither the patients nor the therapists in one group are informed of the patients’ therapeutic process in the other groups and we therefore hypothesize that any contamination will be minor. Furthermore, the exposure toward meals, weight, and shape and Socratic questioning in CFT overlaps substantially with the methods and approach in the CBT. This can possibly confound the comparison, even though we have try to counteract for that by substantially supervision.

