### Power Estimation

A lower-bound probability of detecting effects in clinical research (power) of 0.80 has been suggested (Cohen, 1988). To get some idea of the statistical power in the present study, we estimated the necessary number of observations (*n*) for achieving a power of 0.80 of detecting a medium effect (Cohen’s *d* = 0.5) using an alpha level of 0.05 for three common tests: Calculations of statistical power were performed with G^∗^Power (Buchner and Erdfelder, 1996). All other statistical analyses were conducted with SPSS.

The primary outcomes in the two groups were compared using analysis of covariance (ANCOVA) with pre-treatment values as the covariate. Making the conventional assumptions of no treatment by pre-treatment interaction, this may be formulated as:

(1)$${\text{Post}}_{\text{i}}=\alpha +\beta_{1}^{*}{\text{Treatment}}_{\text{i}}+\beta_{2}^{*}{\text{Pre}}_{i}+\varepsilon_{\text{i}}$$

The treatment-effect may be estimated by the increase in explained variance when including the Treatment effect in the model. Using *d* = 0.5 this corresponds to an increase in *R*^2^ of 0.06. Assuming a rejection criterion (alpha) of 0.05 and a desired power of 0.80 of detecting an increase in *R*^2^ of 0.06, the estimated required sample size is 62 patients per treatment condition.

The design also included a dichotomous “trauma” condition (see section “Introduction”). Reasoning as above the model may be formulated as:

(2)$${\text{Post}}_{\text{i}}=\alpha +\beta_{1}^{*}{\text{Treatment}}_{\text{i}}+\beta_{2}^{*}{\text{Trauma}}_{\text{i}}+\beta_{3}^{*}{\text{(Treatment}}_{\text{i}}^{*}{\text{Trauma}}_{\text{i}}\text{)}+\beta_{4}^{*}{\text{Pre}}_{i}+\varepsilon_{\text{i}}$$

The effect of interest, the Treatment by Trauma interaction, will be estimated by the increase in explained variance when including this effect in the model over a model with all other effects included. Assuming a rejection criterion (alpha) of 0.05 and a desired power of 0.80 of detecting an increase in *R*^2^ of 0.06, the estimated required sample size is 64 patients per treatment condition. The statistical power of the present study with total *N* = 144 thus appears adequate.

As there seems to be no single standard for power analysis within disaggregating between patient effects from the effect of individual patients using longitudinal mixed models, we did not conduct further power, or sample size for this analysis.

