### Treatments

#### Structure

The treatment in both conditions is a multicomponent inpatient program, components including a combination of small groups, individual, and milieu therapy lasting for 13 consecutive weeks, with two of these weeks the patients have a home stay where they practice new behavior. The treatment is closed, that is the patients start and end treatment at the same time and the group is not open to new patients if others end treatment. There are six group therapy sessions each week, altogether 66 group sessions. The duration of group session is 90 min. There are three individual therapy sessions each week, two of them with the individual therapist, and one with the milieu therapist, altogether 33 individual session. The duration of the individual session is 55 min. In these group and the individual sessions, the therapists deliver specific CBT or CFT treatment delivered in accordance with the respective treatment protocols, the manuals for which are available upon request from the first author. In addition to the specific therapy, both groups will participate in physical activity for 90 min and a community group meeting for 60 min each week.

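### Each therapist delivers one treatment only, yet the printed models and the N = 144 power claim treat patients as independent, so the CFT–CBT standard error may be too small and power overstated

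*Protocol article*

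**What the plan says.** **Who treats whom.** Treatment Integrity states: "All therapists will thus have the same training in either CBT or CFT". Each model has its own expert supervisor, and supervision runs until the end of the research period. Under Structure, treatment is given in closed groups, with six group sessions and three individual sessions a week, the latter "two of them with the individual therapist, and one with the milieu therapist".

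**Model.** Statistical Methods names hierarchical linear modelling (HLM) for treatment differences and gives as its reason that all available data can be used. It lists no therapist or group level. Power Estimation says that the primary outcomes are compared by ANCOVA on the pre-treatment value, and prints models (1) and (2), each with one error term per patient.

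**Power.** The setting is described as "Assuming a rejection criterion (alpha) of 0.05 and a desired power of 0.80". For d = 0.5, "this corresponds to an increase in" R² of 0.06. For the main effect "the estimated required sample size is 62 patients per treatment condition"; for the treatment-by-trauma interaction "the estimated required sample size is 64 patients per treatment condition". The section then concludes: "The statistical power of the present study with total" N = 144 appears adequate.

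**Shared staff.** The Discussion says that "the therapist that provide the treatment in the two conditions belong to the same unit" and considers only contamination between the arms. Correlation among patients who share a therapist or a group is not mentioned anywhere.

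**The concern.** Because a therapist works in one arm only, any lasting difference between therapists falls entirely into the CFT–CBT contrast. The continued supervision suggests that the same therapists treat successive intakes. If so, their effects recur in the same arm at every intake and do not average out as more patients are enrolled. A closed group adds a second source of correlation, limited to one intake and arm.

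If patients of the same therapist are correlated, an analysis with one patient-level error understates the standard error of the CFT–CBT main effect, which is the first objective. Differences between a few therapists could then be read as a difference between treatments, and the power attached to N = 144 would be too high. The treatment-by-trauma interaction is less exposed: if each therapist sees patients with and without trauma, a constant therapist effect largely cancels from it.

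**Working it through.** **Inputs from the protocol.** Alpha 0.05, target power 0.80, d = 0.5 (R² increase 0.06), 62 and 64 per arm required, N = 144, so 72 per arm (Power Estimation). Intakes of 16 patients (Design): 144/16 = 9 intakes, about 8 patients per arm in each if split evenly.

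**Assumptions, not in the protocol.** k = 4 to 9 individual therapists per arm with equal caseloads m = 72/k (18 down to 8), and therapist ICC ρ = 0.01 to 0.10.

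**1. The plan's figures reproduce under independence.** Non-central F test with one numerator df and λ = f²N:
- f² = 0.06/0.94 = 0.0638 gives N = 125 (62.5 per arm).
- f² = d²/4 = 0.0625 gives N = 128 (64 per arm).

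At N = 144 the non-centrality is 0.5/√(4/144) = 3.00, and power on 142 df is 0.85.

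**2. Therapist clustering.**
- Design effect: DE = 1 + (m − 1)ρ.
- Type I error of the unadjusted test: 2[1 − Φ(1.96/√DE)].
- Non-centrality: 0.5/√(4·DE/144) = 3/√DE. Power from the non-central t, with 142 df or 2k − 2 df.

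Example, k = 4 and ρ = 0.10: DE = 1 + 17 × 0.10 = 2.70; 1.96/√2.70 = 1.19, so type I error is 0.23; non-centrality is 3/√2.70 = 1.83.

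| k per arm | ρ | DE | Type I error | Power, 142 df | Power, 2k − 2 df |
|---|---|---|---|---|---|
| 9 | 0.01 | 1.07 | 0.06 | 0.82 | 0.78 |
| 9 | 0.02 | 1.14 | 0.07 | 0.80 | 0.75 |
| 9 | 0.05 | 1.35 | 0.09 | 0.73 | 0.68 |
| 9 | 0.10 | 1.70 | 0.13 | 0.63 | 0.58 |
| 4 | 0.01 | 1.17 | 0.07 | 0.79 | 0.64 |
| 4 | 0.02 | 1.34 | 0.09 | 0.73 | 0.58 |
| 4 | 0.05 | 1.85 | 0.15 | 0.59 | 0.46 |
| 4 | 0.10 | 2.70 | 0.23 | 0.44 | 0.34 |

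**3. Margin.** The surplus over 128 is gone at DE = 144/128 = 1.125, that is at ρ = 0.125/(m − 1): 0.018 for k = 9 and 0.007 for k = 4. Against 124 the limit is 144/124 = 1.16.

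**4. Share due to degrees of freedom alone.** With ρ = 0 and 2k − 2 df, power is already 0.71 (k = 4), 0.77 (k = 6) and 0.80 (k = 9).

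**5. Baseline covariate.** Suppose d = 0.5 refers to the unadjusted SD, the pre–post correlation is 0.5 and the residual ICC is 0.02 (all assumed). The non-centrality rises by 1/√(1 − 0.25) = 1.155. Power on 2k − 2 df becomes 0.86 (k = 9), 0.81 (k = 6) and 0.71 (k = 4).

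**6. Are both terms needed?** Type I error was simulated in 20,000 runs with k = 4 per arm, 9 intakes, 8 patients per arm and intake, every therapist active in each intake, and neither covariate nor dropout.

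| Therapist ICC | Group ICC | Patient-level test | Test on group means | Test on therapist means |
|---|---|---|---|---|
| 0.05 | 0 | 0.150 | 0.146 | 0.048 |
| 0 | 0.05 | 0.094 | 0.049 | 0.086 |
| 0.05 | 0.05 | 0.188 | 0.123 | 0.068 |

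Allowing for one source does not remove the other.

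**The case against.** **The levels of the model may be settled elsewhere.** HLM can hold a therapist level, the article does not list its random effects, and the full analysis plan is not at hand. This stands in part: one cannot say that the final analysis will ignore therapists. But the article prints two models without such a term, says that the primary outcomes are compared that way, and draws an adequacy conclusion from them. That conclusion is on the page and rests on independence.

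**The size is assumed.** This stands. With 9 therapists per arm and ICC 0.01, power with patient-level df stays above 0.80. Part of the loss in the last column comes from the degrees of freedom, and the baseline covariate may win some back. A reader might infer from the unadjusted figures that the planned power cannot be reached; the documents do not support that.

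**Some premises are inferred.** The number of therapists, staff turnover and the assignment of patients to therapists are not given. Carry-over between intakes follows from the continued supervision but is not stated. Group sessions outnumber individual ones, so a model with one individual therapist per patient covers only part of the exposure.

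**The remark about the shared unit is about something else.** A reader might take it as an admission of non-independence. It concerns contamination between arms; the point rests on Treatment Integrity, Structure and Power Estimation.

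**Inference to these therapists only.** If therapists are regarded as fixed, type I error is not inflated in that sense. The contrast is then a comparison of two teams, and the article states no such limit.

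**Conclusion.** The point holds in conditional form. The sample-size arithmetic is right under its own premise; the fault is that patients are taken as independent in a design where therapists are nested in arm and treatment is given in closed groups. If patients who share a therapist are correlated, the standard error of the CFT–CBT main effect is too small and the power of N = 144 is overstated.

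Over the assumed range of 4–9 therapists per arm and ICC 0.01–0.10, the design effect is 1.07–2.70. Without covariate gain, power runs from just above the 0.80 target to less than half, against 0.85 under independence. A strong baseline covariate could restore 0.80 at low ICC. The protocol thus supports saying that the target may be missed, not that it will be. The thin margin in step 3 is the firmer statement: with few therapists per arm, an ICC below 0.01 is enough to exhaust it.

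**What to change.** - **Statistical Methods:** specify random effects for individual therapist (nested in arm) and for closed treatment group in the treatment comparisons, with Satterthwaite or Kenward–Roger degrees of freedom.
- **Power Estimation:** say that 62 and 64 per arm, and the adequacy of N = 144, assume independent patients. Restate power at N = 144 for the actual number of therapists over a range of ICC, giving any assumed pre–post correlation.
- **Discussion:** state that, because therapist is nested in treatment, a random effect corrects the standard error but cannot separate therapist from treatment. Conclusions then apply to the treatments as delivered by these therapists.

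**Cost.** Wording, plus a record of each patient's individual therapist and group; the article does not say whether therapist identity is recorded, so this should be confirmed. Confidence intervals will be wider and the power figure less favourable. With few therapists, the variance component will be imprecisely estimated.

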## Data Availability

The datasets that will be generated and/or analyzed during the current study will not be publicly available due to Norwegian laws and regulations, but are available from the corresponding author on reasonable request.

## Ethics Statement

This study was carried out in accordance with the recommendations of the South-Eastern Regional Committee for Medical and Health Research Ethics of Norway (SE-RCE, 2014/836-1) and is enrolled in the international database of controlled trials www.clinicaltrials.gov. The protocol was approved by the SE-RCE. All data will be de-identified by using a unique ID number linked to names. The list of ID numbers and names are only available for the PI, and its destruction upon final data inclusion completely anonymizes all data. All patients will be given written and orally information about the study and must sign an informed consent form in accordance with the Declaration of Helsinki before inclusion in the study. The information will address confidentiality and the patients possibility to withdraw their participation at any time and without clarification. Withdrawing their participation will not affect the treatment. The patients can also refuse to take part in the study, and still receive treatment from Modum Bad. No harm is expected from the treatment. In case of deterioration, the responsible therapist can advise to stop research participation at any time. The patients can address concerns and queries about the study throughout the whole research period to the project leader (KV).

## Abbreviations

AN: anorexia nervosa
BDI-II: beck depression inventory nb 2
BED: binge eating disorder
BMI: body mass index
BN: bulimia nervosa
CBT: cognitive-behavioral therapy
CFT: compassion-focused therapy
CIA: clinical impairment assessment
DSM-5: diagnostic and statistical manual nb. 5
ED: eating disorder
EDE-q: eating disorder examination questionnaire
EDI-2: eating disorder inventory-2
IIP-48: inventory of interpersonal problems
PSS-SR: post traumatic symptom scale self-report
SCL-90: symptom checklist-90
SCS: self compassion scale
WAI: working alliance inventory
